## 3.1 HYPOTHESIS

1. Administration of RMD (5 mg/m^2) to early-suppressed HIV infected individuals and whose CTL response has been refocused to more conserved regions of HIV by HIVconsv therapeutic vaccines will be safe and will reduce the viral reservoir.
2. Both HIV reactivation as well as, in case it is confirmed, eventual toxicity on CTL functionality by RMD, will be related to the exposure to RMD, allowing the definition of a RMD therapeutic range in this specific scenario.
3. After RMD administration, efficient re-stimulation of the cytotoxic response will be reached by MVA.HIVconsv, and the immunogenic response will be associated to the level of immune control after a monitored antiretroviral pause.

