  - 2.5. *In vivo* CTL toxicity assessment based on the most relevant marker from Endpoint 1 (viability, activation, ex) before RMD infusion and after 24 and 72h (RMD1), 12 and 72h (RMD2) and 12, 72 and 7 days (RMD3)
  - 2.6. Development of a population PK/PD analysis to integrate pharmacokinetics of RMD and *in vivo* observed effects of RMD
3. To evaluate the immunogenicity of booster vaccinations with MVA.HIVconsv before and after RMD administration and the effect on viral rebound control after discontinuation of cART.
    - 3.1. To evaluate immunogenicity of booster vaccinations, HIVconsv-specific T cell responses will be measured before, 1, 4 and 8 weeks after both booster vaccinations (MVA1 and MVA2) by IFN $\gamma$  ELISPOT using peptide pools covering different HIV proteins and HIVcons sequences. Total HIVconsv magnitude as well as HIVconsv focus over the rest of HIV-1 specific responses will be compared over time. These results will enable the futility analyses (see section 5.6)
    - 3.2. Evaluation of the effect MVA.HIVconsv boost vaccinations on viral suppressive capacity of CD8+ T cells in vitro, using a flow cytometric assay 4 weeks after MVA2.
    - 3.3. Determine the proportion of individuals who initiate a MAP following the futility analysis
    - 3.4. Determine the proportion of individuals who maintain sustained pVL <2,000 copies/ml during the first 12weeks after treatment cessation.
    - 3.5. Determine the proportion of individuals in whom cART is reinitiated due to viral rebound (2 consecutive pVL >2,000 copies/ml 3-5 days apart), >50% drop in CD4 cell counts, <450 cells/mm^3 and/or symptomatic acute retroviral syndrome.
    - 3.6. Evaluate the emergence of viral resistance during MAP phase
    - 3.7. Evaluate the viral suppression rates 6 months after treatment resumption.

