### 10.1 RESPONSE EVALUATION (EFFICACY)

Two main efficacy endpoints will be evaluated in the BCN02-trial as follows:

Part A) Efficacy of the combined intervention (Kick & kill strategy) in the reduction of viral reservoir will be expressed by total HIV-1 DNA copies per million purified CD4+ T cells measured by quantitative digital droplet PCR (ddPCR) at baseline and 1 week after 3rd dose of RMD. Wilcoxon signed rank test will be used for comparisons.

Part B) Efficacy of HIVconsV vaccines in combination with RMD on viral rebound containment after treatment interruption will be evaluated by analysing the proportion of individuals who maintain sustained pVL <2,000 copies/ml at week 29 (12weeks after treatment cessation). Complementary, a survival analysis will be performed to describe time to rebound during the MAP period. Taking into consideration recent published data suggesting that early treatment initiation could favor a delayed viral rebound/spontaneous viral control in 10% in opposition to <5% in chronically-treated individuals, a positive efficacy signal has been established if at least >20% of individuals remain with pVL <2,000 copies/ml at w12 of MAP (pre-defined efficacy threshold).

Regarding virological and immunogenicity endpoints: Differences in the breadth and magnitude of different virological and immune parameters analyses between two longitudinal determinations in the same individuals will be assessed using a Wilcoxon signed-rank test. Correlations between the virologic, immune parameters and clinical outcome will be performed using Pearson test.

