## 10.2 SECURITY ANALYSIS

In addition to safety description analysis, stopping rules will be established for the two parts of the study as follows:

a) Stopping rules during the Part A of the study will be based on the observation of an unexpected high proportion of individuals experiencing any AE/SAE to any of the vaccinations and/or RMD administration as described in section 5.6.

b) On the other side and in order to minimize risks of the intervention, an early interim and futility analyses is planned for each individual before the MAP phase. Acceptability for cART interruption after interim analyses will be reviewed. Treatment interruption would be discouraged individually if a) boosting MVA.HIVconsv was shown to be no longer immunogenic after RMD administration (no net increase in induced response compared to pre-vaccination levels with MVA.HIVconsv at BCN02-Romi baseline visit) and/or b) persistent detectable viremia. Limited MVA.HIVconsv immunogenicity after MVA2 may indicate RMD toxicity on CTL functional activity for instance; therefore, an improved viral control would not be foreseen. On the other hand, increases in immune activation shortly after immunization are expected to decrease 8 weeks after vaccination. However, in some cases, intermittent detectable plasma low-level viremia have also been reported to occur after vaccination, which may induce an extended immune activated status that could favor a faster and higher viral rebound after treatment cessation. Therefore, clinical team will discuss cases where treatment interruption could be also discouraged in cases with persistent detectable viremia (i.e. longer than 12 weeks after last immunization)

In all cases where immune and/or virological futility criteria are not met and treatment interruption is discouraged, trial results would be focused on the viral reservoir and immunogenicity endpoints only until better correlates of control would be available to predict clinically relevant outcomes on which one could recommend treatment interruptions in a safer manner.

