### 10.3 SAMPLE SIZE DESCRIPTION

Individuals that participated in the BCN01 trial and which are followed in the extension phase (BCN01-RO) will be offered to participate in the study. Therefore, the trial will enroll a maximum number of 24 subjects. The primary endpoint of the study is safety and tolerability of the combined kick & kill strategy in recently HIV-1-infected individuals under early suppressive therapy. In terms of total number of individuals exposed to each MVA.HIVcons vaccine and confidence intervals to detect an AE (i-e- based on published results the probability of experiencing a grade 3 or 4 AE is thought to be <0.1). Information on expected rates of AEs related to RMD at the clinical dose proposed is still scarce. The trial has been designed as a pilot study and will only allow detection of a large effect among participants. However, the incidence of grade  $\geq 3$  or SAEs will be used as a measure of safety of the experimental strategy.

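### The Part B >20% signal appears to be read among people selected to pause cART, yet it is set against a 10% reference with no such selection, and the denominator is not named

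*Protocol*

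**What the plan says.** Section 10.1, Part B, fixes the decision rule: "a positive efficacy signal has been established if at least >20% of individuals remain with pVL <2,000 copies/ml at w12 of MAP". Its stated basis is that "early treatment initiation could favor a delayed viral rebound/spontaneous viral control in 10% in opposition to <5% in chronically-treated individuals". The related secondary endpoint (5.3.2, item 3.4) is worded as "Determine the proportion of individuals who maintain sustained pVL <2,000 copies/ml during the first 12weeks after treatment cessation". Neither place names a denominator. References to treatment cessation and to week 12 of the MAP suggest those who paused.

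Who pauses is decided person by person:

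- **Immune criterion (7.3.4, 10.2).** The pause is discouraged if the second boost brings no net rise in HIVconsv response over the BCN02 baseline, because improved control is then not expected.
- **Viraemia criterion (7.3.3, 8.1.14, 10.2).** The pause is postponed until two consecutive undetectable results. Section 10.2 adds that it may be discouraged if viraemia persists, "which may induce an extended immune activated status that could favor a faster and higher viral rebound after treatment cessation".
- **Consequence (10.2).** Where "treatment interruption is discouraged, trial results would be focused on the viral reservoir and immunogenicity endpoints only".

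Hypothesis 3 (section 3.1) expects that "the immunogenic response will be associated to the level of immune control after a monitored antiretroviral pause". Endpoint 3.3 in section 5.3.2 is to "Determine the proportion of individuals who initiate a MAP following the futility analysis", so the plan allows for some participants not pausing. Section 5.2, by contrast, says the MAP is offered to all participants.

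Section 10.3 states that "the trial will enroll a maximum number of 24 subjects". The trial has a single arm. No section adjusts the 10% or the 20% for selection before the pause.

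**The concern.** A single-arm proportion can be compared with an outside rate only if both describe the same kind of people. Here the 10% is given for early-treated individuals as a group. The observed proportion appears to come from the subset who responded to the boost and were aviraemic before stopping cART. If people who would control anyway are more likely to meet those criteria, the proportion among pausers rises without any effect of vaccine or romidepsin on rebound.

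The rule in 10.1 would read that rise as efficacy of the strategy. Part B has no concurrent control, so the contrast with 10% is its only yardstick for rebound, and nothing else in Part B would reveal the shift.

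**Working it through.** **Inputs.** From the protocol: threshold >20% and reference 10% (10.1), at most 24 enrolled (10.3). The protocol gives no pass rate, so the number pausing is an assumption: 18 of 24, with 22 and 15 as alternatives. The true control rate is set at 10%, with no intervention effect on rebound. The plan derives no alpha or power for this rule, so there is no figure of its own to reproduce.

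**Count needed.** More than 20% of m people means at least floor(0.2m) + 1 controllers:

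- m = 24: 0.2 × 24 = 4.8, so 5
- m = 22: 4.4, so 5
- m = 18: 3.6, so 4
- m = 15: 3.0, so 4

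**Everyone treated as denominator.** P(Bin(24, 0.10) ≥ 5) = 8.5%.

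**18 pause, 6 do not (pass fraction 18/24 = 0.75):**

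- *Criteria unrelated to control.* P(Bin(18, 0.10) ≥ 4) = 9.8%.
- *Controllers fail half as often as others.* Let non-controllers fail with probability g and controllers with g/2. Then 0.10 × g/2 + 0.90 × g = 0.95g = 0.25, so g = 0.263 and g/2 = 0.132. The rate among pausers is 0.10 × (1 − 0.132)/0.75 = 11.6%, and P(Bin(18, 0.116) ≥ 4) = 14.7%.
- *Extreme: every controller pauses.* All controllers among the 24 are in the numerator, so P(Bin(24, 0.10) ≥ 4) = 21.4%.

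**Other numbers pausing:**

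| Pausing of 24 | Controllers needed | Unrelated | Half as often | No controller lost |
|---|---|---|---|---|
| 22 | 5 | 6.2% | 7.2% | 8.5% |
| 18 | 4 | 9.8% | 14.7% | 21.4% |
| 15 | 4 | 5.6% | 11.6% | 21.4% |

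The unrelated column moves up and down because the required count changes in whole steps. The effect of selection is the rise across each row.

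**Expected rate among pausers.** At the extreme it is 0.10 divided by the pass fraction: 0.10/0.75 = 13.3% with 18 pausing, and 20% with half pausing. The expected rate exceeds 20% only if more than half do not pause and no controller is lost. Short of that, crossing 20% also needs chance.

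**The case against.** The strongest objection concerns what the immune criterion measures. The protocol says *improved* control is not expected after a failed boost, possibly because romidepsin harmed CTL function. That describes loss of added vaccine benefit, not a lower spontaneous control rate. If the boosted response has no bearing on rebound, this criterion need not sort natural controllers at all, and the unrelated figures apply. If it does bear on rebound, part of the enrichment is real intervention effect. This stands as a limit on size. Without a control arm, though, the pauser rate cannot separate vaccine effect from a natural capacity to respond. The viraemia criterion has a stated link to faster rebound that does not run through vaccine benefit.

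The text is also softer than exclusion. The pause is discouraged rather than barred, viraemia mainly delays it, and 5.2 offers the MAP to all. A reader might infer that the signal definitely counts only those who met the criteria. The documents do not say so: the pauser denominator is an inference. Defining analysis sets is often left to a SAP, but here the protocol itself fixes the decision rule and its reference.

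Part B is secondary in a declared pilot, time to rebound is also described, and reservoir reduction is a separate primary endpoint. Endpoint 3.3 will show how many paused. All true, and all reasons for a modest correction.

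Finally, an all-treated rule has a price. With 18 pausing and a true 30% among them, requiring 5 controllers instead of 4 lowers the chance of a signal from 83.5% to 66.7%. With 15 pausing it falls from 70.3% to 48.5%. This argues against making the all-treated rate the sole decision rule, but not against reporting it.

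**Conclusion.** The point holds as a mismatch between a possibly favourably selected group and an unselected reference, made worse by an unnamed denominator. Its size cannot be fixed from the protocol. With 24 enrolled, 18 pausing and a true 10% rate, the false-signal chance lies between 9.8% and 21.4% depending on how strongly the criteria track control, against 8.5% when all 24 are counted. With 2 not pausing it is at most 8.5%, against 6.2% without selection.

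A reader might infer that the criteria by themselves carry the rate past 20%. The documents do not support that: in expectation it needs more than half not pausing and no controller lost. The 21.4% is an upper extreme, not a forecast.

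**What to change.** In section 10.1, Part B:

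1. Name the denominator of the >20% rule.
2. Report, each with an exact confidence interval, the proportion among MAP starters and the proportion among all who received the intervention (for example, the first MVA boost and at least one romidepsin infusion). In the second, count those who did not pause as not shown to control.
3. State that an excess over 10% seen only among MAP starters comes from a selected subgroup and is not by itself a positive signal against the unselected reference.

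The cost is a few sentences and one extra proportion from data already collected under endpoints 3.3 and 3.4. The drawback is that the all-treated proportion is conservative, because the rebound outcome of those who did not pause is unobserved. The text should say so. No rule on who pauses is changed.

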### 10.3 SAMPLE SIZE DESCRIPTION

Individuals that participated in the BCN01 trial and which are followed in the extension phase (BCN01-RO) will be offered to participate in the study. Therefore, the trial will enroll a maximum number of 24 subjects. The primary endpoint of the study is safety and tolerability of the combined kick & kill strategy in recently HIV-1-infected individuals under early suppressive therapy. In terms of total number of individuals exposed to each MVA.HIVcons vaccine and confidence intervals to detect an AE (i-e- based on published results the probability of experiencing a grade 3 or 4 AE is thought to be <0.1). Information on expected rates of AEs related to RMD at the clinical dose proposed is still scarce. The trial has been designed as a pilot study and will only allow detection of a large effect among participants. However, the incidence of grade  $\geq 3$  or SAEs will be used as a measure of safety of the experimental strategy.

### 10.4 DEVIATION OF STATISTICAL PLAN

Any deviation from that presented statistical plan will be described and justified in the final report.

## 11 DIRECT ACCESS TO SOURCE DATA/DOCUMENTS

Researchers and institutions will allow the monitoring, and audits by the Health Authorities or the Sponsor giving direct access to data and original source documents.

Access to personal patient information will be restricted to the Study physician / staff. To allow monitorings, audits and inspections, access to data to Health Authorities (Spanish Agency for Medicines and Health Products), the Ethics Committee and personnel authorized by the Sponsor, is guaranteed while maintaining the confidentiality thereof according to current legislation.

## 12 QUALITY CONTROL AND QUALITY ASSURANCE

### 12.1 STUDY MONITORING

In accordance with applicable regulations and Good Clinical Practice (GCP), the monitor will visit or contact the center on a regular basis. The duration, nature and frequency of visits / contacts depend on the monitoring plan.

During these contacts, the monitor shall:

- monitor and evaluate the progress of the study;
- examining the data collected;
- carry out a verification of the source documents;
- identify any problems and find solutions;

The goal of the monitoring activity is to verify that:

- the rights and welfare of subjects are respected;
- survey data are accurate, complete and verifiable with the help of original documents;
- the study is performed according to the protocol and any amendment adopted, GCPs and regulations.

The investigator must agree to:

- grant to monitor direct access to all relevant documentation;
- devote part of his/her time and staff time to the monitor in order to discuss the results of the monitoring, as well as any other possible aspect.

The monitor should also contact the center before starting the study with the aim to discuss with staff the Protocol and procedures for data collection.

### 12.2 AUDITS AND INSPECTIONS

Sponsor can carry out an audit of quality control at its sole discretion. In this case, the investigator should agree to grant the auditor direct access to all relevant documentation and devote part of his/her time and staff time to the auditor in order to discuss the results of the monitoring, as well as any other possible aspect.

Moreover, regulatory authorities may also inspect the study. In this case, the investigator should agree to give the inspector direct access to all relevant documentation and devote part of his/her time and staff time to the inspector in order to discuss the results of the supervision, as well as any other possible aspect.

### 12.3 CASE REPORT FORM

Data collection will be done through an electronic CRF with a system of access by username and password. The application has track changes (recording the user that has performed).

Accurate and reliable data collection is ensured by checking and cross checking the CRF front site records conducted by the study monitor (verification of source documents). The data collected will be added to a computer database which will be reviewed for possible inconsistencies to be resolved by the research team of the study in each site.

The content of the CRF is attached in Attachment Q

## 13 ETHICS

### 13.1 GENERAL CONSIDERATIONS

The clinical trial will be conducted according to the principles of the Declaration of Helsinki, Fortaleza, Brasil, octubre 2013.

This study will be conducted according to Spanish regulations and the required documentation prior to the start will be:

- Protocol acceptance by the sponsor and the coordinating investigator
- Protocol approval by the Ethics Committee.
- Protocol authorization from the Spanish Drug Agency (Ministry of Health)

All subjects will be guaranteed continued medical and nursing supervision throughout the duration of the study.

This study will conform to the standards of "Good Clinical Practice".

Also, following the "Good participatory practice guidelines" (published by the Joint United Nations Programme on HIV/AIDS (UNAIDS)), representatives of the community-based detection centres have participated in the design of the protocol and the Participant Information Sheet, through the Community Advisory Committee (CAC).

### 13.2 PATIENT INFORMATION SHEET AND INFORMED CONSENT

Informed consent will be obtained before including the patient in the trial. The investigator is to inform the patient of the nature, duration and purpose of the study, as well as of all the obstacles and inconveniences which – within reason – may be expected from it. Furthermore, the patient is to receive information in writing. The participating patients must be legally competent to give informed consent, with the possibility of taking decisions at his/her own free will. The patient has the right to leave the study at any time.

Patient information sheet (PIS) and informed consent form (ICF) may be found in attachment R.

### 13.3 PAYMENT TO RESEARCH SUBJECTS

Volunteers will be reimbursed for their time, effort and time travels to study sites due to study participation. Reimbursement amounts will be documented in the PIS.

A payment of € 500 for meals, transfers and lost in productivity is foreseen and will be set in two times:

- € 200 at the end of first phase
- € 300 at the end of the second phase

Additionally, a free taxi service will be offered to patients for vaccination and romidepsin administration visits performed in UPIC. Particularly, service will be offered for journeys to Hospital Universitari Germans Trias i Pujol (HGTIP) in visits MVA1, RMD1, RMD2, RMD3 and MVA2 and return journeys in visits RMD2 and RMD3.

## **14 DATA HANDLING AND RECORD KEEPING**

### **14.1 DATA HANDLING**

The processing of the data to be compiled by the study sponsor during the trial will be subject to current legislation as regards data protection (LOPD, Ley Orgánica 15/1999, de 13 de diciembre de protección de datos de carácter personal). The patient will be identified in the records by the corresponding code number only. The patient is to be guaranteed anonymity, and is to be informed that all communication will take place between him/her and the investigator – not the sponsor of the trial.

Data transmitted to third countries and other countries will in no case contain personal data. In the event that such transfer occurs, it will be for the same purposes of the study described and ensuring confidentiality at least to the level of protection of the law in Spain.

### **14.2 RECORD KEEPING**

#### **14.2.1 Investigator file and document retention**

The investigator must keep the investigator file with the proper and accurate records to enable the study to be fully documented and data subsequently verified.

The Investigator's study file will contain the protocol and its amendments, CRFs, questionnaires' forms, EC approval and authorization from the health authorities, samples of the patient information sheet and informed consent, staff curriculum, signatures' delegation log and listing of subjects, as well as other appropriate documents and correspondence.

Clinical source documents from subjects (usually predefined by the project to record key efficacy and safety parameters or documents that are not in the clinical record of the hospital) will be filed indicating the number of patient without personal data.

The investigator should retain these documents at least five years, according to SCO/256/2007, provided that the promoter does not express a greater period.

